## Abstract

**Background:**

In the last few years, excessive internet use and computer gaming have increased dramatically. Salience, mood modification, tolerance, withdrawal symptoms, conflict, and relapse have been defined as diagnostic criteria for internet addiction (IA) and computer addiction (CA) in the scientific community. Despite a growing number of individuals seeking help, there are no specific treatments of established efficacy.

**Methods/design:**

This clinical trial aims to determine the effect of the disorder-specific manualized short-term treatment of IA/CA (STICA). The cognitive behavioural treatment combines individual and group interventions with a total duration of 4 months. Patients will be randomly assigned to STICA treatment or to a wait list control group. Reliable and valid measures of IA/CA and co-morbid mental symptoms (for example social anxiety, depression) will be assessed prior to the beginning, in the middle, at the end, and 6 months after completion of treatment.

**Discussion:**

A treatment of IA/CA will establish efficacy and is desperately needed. As this is the first trial to determine efficacy of a disorder specific treatment, a wait list control group will be implemented. Pros and cons of the design were discussed.

**Trial Registration:**

ClinicalTrials (NCT01434589)

## Background

The internet has become accessible for the great majority of the population (for example flat rates, WLAN, or portable computers). In a representative German sample (n = 2475) in 2009 the rate of leisure-time internet users for women was about 51% and for men about 60%. The most frequently used internet applications were email (93%), information and research (92%), shopping (76%), and chatting (62%) [1]. In 2004 about 68% of American adults used the internet regularly and 4% to 14% showed one or more markers of problematic use with a prevalence of internet addiction (IA) at about 1% [2], which is concordant with an actual German study [3]. The onset of manifest addicted behavior is reported in the late 20s or early 30s age groups [2]. In epidemiological studies, prevalence rates of addicted internet use and computer game behavior range between 1.5% to 3.0% in German [3,4] and Austrian [5] adolescents, respectively.

According to Block [6], three subtypes of IA/computer game addiction (CA) (excessive gaming, sexual preoccupations, and email/text messaging) have four components in common: (a) excessive use (along with a loss of sense of time or the ignorance of basic drives); (b) withdrawal (for example tension, anger, agitation, and/or depression when access to a computer is blocked; (c) tolerance (increasing use or sophistication of computer equipment); and (d) negative repercussions (for example poor achievement/performance, fatigue, social isolation, or conflicts).

Salience, mood modification, tolerance, withdrawal symptoms, conflict, and relapse are additional diagnostic criteria for IA and CA [7]. The addicted individual is increasingly attracted towards the excessive behavior and life is emotionally and cognitively preoccupied with the application (for example computer game), requiring more and more time in order to regulate his mood states. Empirical studies [4,8,9] have demonstrated that the symptom complex of IA/CA [10,11] matches the criteria of substance disorders. Results of neurobiological studies have identified neurophysiological mechanisms in IA/CA equivalent to substance abuse (alcohol [12] and cannabis addiction [13]).

## Methods/Design

### Study centers

This multicenter study is coordinated by the outpatient clinic for behavioral addictions of the Clinic for Psychosomatic Medicine and Psychotherapy of the University Medical Center Mainz. Three centers will further participate, the Anton-Proksch-Institute, Austria, the Section Addiction Medicine and Addiction Research of the University Hospital Tübingen, and the Addiction Medicine of the Central Institute of Mental Health in Mannheim.

Investigators in all centers are psychotherapists (physicians or psychologists) and experts in the treatment of addiction behavior.

### Participants

Patients will be included, if the following eight inclusion criteria are fulfilled: (1) IA/CA according to the AICA (Assessment of Internet and Computer game Addiction) expert rating for at least 6 months and (2) a score ≥ 7 in the AICA self-report IA/CA. (3) Patients with co-morbid disorders will be included, provided that IA/CA is the primary diagnosis. The study will only include (4) men in (5) the age between 17 and 45 years. (6) If the patients are currently on psychotropic medications, no changes in medications and dosages in the past 2 months and during STICA treatment are allowed. (7) If currently off all psychotropic medications, patient must have been off at least 4 weeks. (8) During STICA no other ongoing psychotherapy is allowed and previous psychotherapy must have been completed for at least 4 weeks.

Patients with a score <40 in the Global Assessment of Functioning (GAF [28]) or severe major depression (Beck Depression Inventory; BDI-II [29] ≥ 29) are excluded. Additional exclusion criteria are current alcohol or drug addictions, borderline, antisocial, schizoid, and schizotypal personality disorders, a lifetime diagnosis of schizophrenia, schizoaffective, bipolar, or organic mental disorder and a current unstable medical illness.

Over a time period of 36 months we plan to include 192 patients in the study. The patients will be randomly assigned to the intervention or to the wait list control group (WLC). Prior to randomization, a total of 18 patients have to be allocated to the trial. The intervention group will start treatment immediately after randomization, whereas the WLC group has to wait over a period of 4 months, until they will receive the same therapy.

### Intervention

The manualized STICA [26] is based on a cognitive behavior approach and combines group with individual therapy. STICA comprises 23 psychotherapy sessions with a total duration of 4 months. Fifteen out of twenty-three sessions will be weekly group sessions (100 min each) and eight will be fortnightly individual sessions (50 min).

Table 1 shows treatment phases and strategies during the early, middle, and termination phases. Based on understanding the mechanisms and the consequences of IA/CA (early phase), patients are trained to identify the triggers of their own dysfunctional internet use. By using diaries, social skill training, and exposition training, patients learn to reduce and to control their computer and internet use. In the termination phase of treatment, tools will be transferred to daily life and strategies for relapse prevention will be discussed.

**Table 1 T1:** STICA Treatment phases and strategies

**Treatment phase**	**Key interventions**
Early phase	Patient education on mechanisms and effects of IA/CA (for example learning theories, development and consequences of IA/CA, vicious cycles of addiction, and so on)
	Promotion of social communication and bonding in the group and individual setting
Middle phase	Identification of the triggers of dysfunctional internet use (for example emotional states, maladaptive cognitions, daily hassles, and so on) by keeping diaries
	Functional analysis of the addictive behavior
	Enabling functional internet use by appropriate problem-solving strategies
	Assisting the establishment of a social network in real life
	Building alternative activities
	Self-monitoring to reduce procrastination tendencies
	Promotion of social communication
	Exposition training (confronting and deleting access to critical applications, for example the self-created avatar)
	Skill training (for example coping with stress and problems, social skills, building alternative activities, and so on)
	Promotion of functional computer and internet use
Termination and relapse prevention	Review of transfer of treatment tools to daily life
	Functional computer/internet use
	Elaboration of tools preventing a relapse

**Figure 1 F1:**
[figure not shown]
**Flow chart of the study.** Patients of the wait list control group (WLC) will be offered STICA treatment after the intervention group has finished. The follow-up analysis will be performed separately for WLC.

The assessment T0b is performed immediately before randomization and commencement of treatment. The criteria for IA/CA will be rechecked by self-report measurements, if the delay due to the group recruitment exceeds 2 weeks. Therapists fill out the GAF [28] and collect information about medications, other therapies, and treatment history. An independent and blinded rater will assess mental disorders with the SCID-I/II [32] and conduct the AICA-Checklist. A drug screening is further used to assess objective information on drug consumption. Self-report assessment includes IA/CA (AICA-S [30,31]), depression (BDI-II [29]), obsessive-compulsive behavior (SCL-90-R [33]), generalized anxiety and panic (Patient Health Questionnaire [34]), somatization [34], general distress [34], depersonalization (CDS-2 [35]), and social fear (LSAS [36]). Patients also fill out dimensions of personality (NEO-FFI [37]), attention deficit disorder (WURS-k [38]), self-efficacy (SWE [39,40]), positive and negative affectivity (PANAS [41]), and adverse childhood experiences (ACE [42]). Finally, they answer questions concerning perceived stress (PSS [43]) and about their life satisfaction (FLZ [44]). Attention of the patients will be checked with the d2 [45].

After 2 months of therapy (T1) patient-rated outcome measures are reapplied (AICA, GAF, BDI-II) and drug screening repeated. The outcome measures are supplemented by assessments of group climate (GCQ [46]) and therapeutic alliance (HAQ [47]).

Immediately after completion of the intervention (T2) patients fill out a set of questionnaires identical with the set at T0b, except for the trait measures (NEO-FFI, WURS-k, ACE). Group climate and therapeutic alliance are assessed additionally. Drug screening is applied and is obligatory. For patients of the WLC group this is the final assessment. Shortly after the survey their intervention will start.

Patients of the intervention group are asked to evaluate the stability of treatment effects 6 months after termination of treatment (T3). Thereby the used set of questions corresponds to T2.

### Data collection

In this study there are two sources of electronic study data. An eCRF has been developed for the investigators to document their study data in a database stored, maintained, and administered by the IZKS Mainz. It is password protected with individual accounts for all investigators.

Patients will answer the self-report questionnaires by entry forms customized for iPADs. Each patient receives only access to his own current questionnaire.

After data collection, eCRF and iPAD data will be transformed into one SAS database for evaluation.

### Objectives and hypotheses

The purposes or this study are to determine the efficacy of STICA, to assess the durability of treatment response in these patients, and the impact on associated mental symptoms (for example social anxiety and depression).

### Outcomes

The primary efficacy endpoint is defined as improvement of IA/CA rated by the patient himself (primary outcome measure: AICA-S [30,31]). At the end of therapy an AICA-S score <7 indicates remission.

Secondary endpoints include the remission of IA/CA in the expert rating (AICA-C ≤ 13). The preoccupation with the internet or computer games will be analyzed (hours spent per week). IA and CA are associated with negative consequences in health, social communication, psychosocial wellbeing (GAF [28], BDI-II [30], LSAS [36]), level of performance in school or work, and self-efficacy (SWE [39]). For each instrument assessments at baseline will be compared to assessments obtained 4 and 6 months after therapy.

### Sample size calculation

The sample size calculation is based on the primary endpoint (T2: end of therapy) and a chi-square test without continuity correction on a two-sided level of significance of 0.05. The calculation is based on results from 33 patients, who participated in an open trial. Twenty-four patients improved according to the AICA-S < 7. A difference to the control group of 20% is considered as clinically relevant. With a power of 90%, 184 patients in total are needed to detect that difference. Considering the average therapy group size of eight, 16 subjects have to be randomized at the same time. Therefore, we will need to include 192 patients in this trial (*n* = 96 patients for each group). The primary analysis will be performed on the population of all randomized subjects (intention to treat (ITT) population). Subjects who discontinue the therapy will be regarded as non-improvers to treatment. Our previous experience with internet addicts revealed drop-out rates of about 27% (nine drop-outs from 33 patients).

### Randomization

Patients will be randomly assigned either to the STICA intervention group or to the WLC group. The randomization list will be generated stratified by the Interdisciplinary Centre for Clinical Trials (IZKS). Considering the average therapy group size of eight patients, 16 patients have to be randomized at the same time. The randomization ratio will be 1:1 within each center. After confirmation that a patient fulfils all inclusion criteria for randomization, the electronic case report form (eCRF) will immediately provide the investigator with the randomization results. Patients are subsequently informed about the randomization result and the intervention starts shortly after randomization. The IZKS will furthermore insure treatment integrity by regular site visits.

### Statistical analysis

#### Primary analysis

The primary efficacy endpoint is defined as the change of the AICA-S level. This will be analyzed using a logistic regression model with predictors of group (STICA treatment *vs.* WLC), pre-treatment score of AICA-S, education, trial center, and age.

The primary hypothesis to be tested is:

H_0_: π_STICA_ = π_WLC_*vs.* H_1_: π_STICA_ ≠ π_WLC_

where π_STICA_ and π_WLC_ are the probabilities to respond to treatment in the STICA treatment group and the WLC group, respectively. The primary analysis will be performed on the ITT population on a two-sided level of significance α = 0.05. The two-sided level of significance will be the same for all analyses. A completer analysis will be performed for sensitivity. Additionally, the analysis will be repeated with a predictor for the therapy group. Drop-outs during the treatment phase will be regarded as treatment failures.

#### Secondary analysis

The remission of IA/CA according to the AICA Checklist will be examined using logistic regression analyses with the same predictors as the primary analysis. The reduction of negative consequences, GAF, depression (BDI-II), and social anxiety (LSAS) will be examined using ANCOVA with covariates.

Analyses will be conducted on a two-sided level of significance of α = 0.05. Descriptive statistics are used to show changes over time. Serious adverse events and drop-outs will be analyzed by using descriptive statistics.

### Safety aspects

Safety parameters will comprise newly occurring psychiatric diagnoses (SCID-I [32]) and all serious adverse events that are reported during and up to 6 months after treatment. Therefore in the context of psychotherapy suicidal ideations or the global functioning level will be regarded.

### Medical complications

According to GCP, an adverse event (AE) is defined as follows: any untoward medical occurrence in a patient participating in a clinical trial. An AE can therefore be any unfavorable and unintended sign (including an abnormal laboratory finding), symptom, or disease, whether or not related to the trial intervention. Due to the fact that this trial analyses a psychological treatment, only AEs concerning psychological conditions, defined as any disorder classified by the International Classification of Diseases [48] F00-F99 (‘Mental and Behavioral Disorders’) will be documented.

For this study the following conditions were defined as AE: (1) new symptoms/medical conditions, (2) new diagnosis, (3) intercurrent diseases and accidents, (4) worsening of medical conditions/diseases existing before clinical trial start, (5) recurrence of disease, or (6) increase of frequency or intensity of episodical diseases.

A serious adverse event (SAE) is an AE that: (1) results in death, (2) is life-threatening, (3) requires patient hospitalization or prolongation of existing hospitalization, (4) results in persistent or significant disability/incapacity, or (5) is a congenital anomaly/birth defect.

All medical complications during the study are documented in the eCRF.

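### The protocol contradicts itself on which adverse events are recorded, and does not say whether its F00-F99 limit applies to serious adverse events

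*Protocol article*

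**What the plan says.** Five statements in the protocol article bear on what is recorded. The first four are in Medical complications, in this order.

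- **General definition.** An adverse event is "any untoward medical occurrence in a patient participating in a clinical trial", whether or not related to the intervention.
- **Recording limit.** Because the treatment is psychological, "only AEs concerning psychological conditions, defined as any disorder classified by the International Classification of Diseases [48] F00-F99" are to be documented.
- **Study-specific list.** Six kinds of event count as adverse events for this study. The third is "intercurrent diseases and accidents"; the fourth reads "4) worsening of medical conditions/diseases existing before clinical trial start". No item repeats the F00-F99 limit.
- **SAE definition and closing rule.** "A serious adverse event (SAE) is an AE that: (1) results in death", or meets one of four further criteria: threat to life, hospitalization, lasting disability, or congenital anomaly. The section ends: "All medical complications during the study are documented in the eCRF".
- **Safety aspects.** The safety parameters are newly occurring psychiatric diagnoses and "all serious adverse events that are reported during and up to 6 months after treatment". Suicidal ideation and global functioning are also to be considered.

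Elsewhere, Secondary analysis plans descriptive statistics for SAEs, and Ethical issues requires that study-related SAEs be reported immediately to the monitoring board and the ethics committee.

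**The concern.** An investigator whose patient is admitted to hospital after a road accident needs to know whether to complete a form. The recording limit says no. The study-specific list and the closing rule say yes. The SAE definition does not settle it, because it is built on the adverse event definition and says nothing about the limit.

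What is at stake is the completeness and comparability of the SAE data. SAEs are a named safety parameter and will be tabulated. With one coordinating and three further centers, each may follow a different sentence in good faith, and a difference in SAE counts between centers could then reflect recording practice rather than patients' experience.

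A second uncertainty concerns the arms. The randomized comparison covers the 4 months in which one arm is treated and the other waits. If SAE collection is tied to treatment, it is unclear whether the waiting arm is observed on the same terms.

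**Working it through.** No arithmetic underlies the contradiction. The check is to set the sentences side by side and ask whether one consistent rule can be read out of them.

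**Step 1: can the list be read as lying inside the limit?** One could take the six items as kinds of psychiatric event, all within F00-F99. That works for a new diagnosis or a recurrence. It fails for the third item, since an accident is not a mental or behavioural disorder. It is strained for the fourth, which speaks of medical conditions generally.

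**Step 2: can the closing rule be read as lying inside the limit?** One could take medical complications to mean only those adverse events that survive the limit. The closing sentence would then add nothing, and the conflict with the third item would remain.

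**Step 3: does the SAE definition escape the limit?** An SAE is an adverse event that meets a seriousness criterion. The limit concerns which adverse events are documented, and no exception for serious ones is stated. Congenital anomaly, which is not a mental disorder, is nevertheless among the criteria, so the SAE list does not match the limit.

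**Step 4: what each reading would record.**

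| Event | Limit governs everything | Limit governs non-serious events only | Closing rule governs |
|---|---|---|---|
| New depressive episode, not serious | recorded | recorded | recorded |
| Somatic illness, not serious | not recorded | not recorded | recorded |
| Accident with hospital admission | not recorded | recorded | recorded |
| Death from a non-psychiatric cause | not recorded | recorded | recorded |

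Each column has support in the text, and none agrees with all of it. The last two rows matter most: one reading loses serious events that the other two keep.

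**Step 5: the time window.** Under Participants, the intervention arm starts treatment immediately after randomization and the wait list arm waits 4 months. Under Intervention, treatment lasts 4 months. Counting months from randomization and taking Safety aspects literally:

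- STICA arm: from month 0 to month 4 + 6 = 10.
- Wait list arm: from month 4 to month 4 + 4 + 6 = 14.

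On that reading, months 0 to 4 are covered in the STICA arm but not in the wait list arm. With 96 planned control patients, the control time in question is at most 96 × 4 = 384 patient-months. The closing rule in Medical complications speaks of the whole study, and control patients are in the study from randomization, so that sentence points to coverage. The two sentences need to be aligned.

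**The case against.** The strongest reply is that the text contains enough to capture serious events. The F00-F99 sentence limits documentation and does not redefine an adverse event. On the general definition and the list, a fatal accident is an adverse event and hence an SAE; Safety aspects counts all reported SAEs without an ICD limit; and the closing rule covers every complication. Limiting non-serious events in a psychotherapy trial is a reasoned choice, and operational detail belongs in the full protocol, which is not shown.

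Much of this stands, and it rules out several stronger conclusions that a reader might draw:

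- **That accidents and non-psychiatric deaths are definitely excluded.** The document does not settle this. Its sentences point both ways, so such events can be lost but need not be.
- **That self-harm falls outside recording.** This would require knowing how an attempt is coded. The article gives no coding rule for self-harm and never names it. Suicidal ideation is named under Safety aspects, so suicidality is not ignored.
- **That the whole waiting period is unmonitored.** This follows only from the literal reading in Step 5. No sentence excludes the wait, and control patients are assessed at its end.
- **That the monitoring board lacks comparable counts by arm.** The article does not say what tabulations the board receives.

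The reply does not remove the conflict. An event that is an SAE by definition is still lost if the recording rule tells the site not to document it. Safety aspects counts only what is reported, so it does not lift the limit. Nor is this a case of detail left to a fuller document: the article states rules that disagree.

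**Conclusion.** The point holds as a contradiction in stated recording rules. Medical complications restricts documentation to F00-F99, then includes accidents, intercurrent illness and worsening medical conditions, and then promises to document everything. With SAEs defined through adverse events and no exemption given, non-psychiatric deaths, hospital admissions or accidents can go unrecorded, or be recorded differently by center, depending on which sentence is followed. The SAE window fits the wait list arm poorly; this is a secondary ambiguity, not an established gap.

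The size in events cannot be derived, because the document gives no expected SAE rate. The uncertainty applies to all 192 planned patients, but that is the population concerned, not an estimate of loss. Safety data are analyzed descriptively, and the primary efficacy analysis is unaffected. The conclusion rests on the article's wording alone; the full protocol or eCRF instructions may already resolve it. It should be corrected, but it does not threaten the trial's main result.

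**What to change.** Reconcile Medical complications and Safety aspects under one rule:

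1. Apply the F00-F99 limit to non-serious adverse events only, and say so in the sentence that introduces it.
2. Record every SAE regardless of ICD chapter, stating that this includes any serious self-harm, so that recording does not depend on coding.
3. Collect SAEs from randomization in both arms, including the 4-month wait, and state the end of collection for each arm.
4. Reword the third item of the adverse event list and the closing sentence to match.

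The cost is a change of wording, matching eCRF instructions and a few additional SAE forms. The design, sample size and efficacy analysis do not change, and the economy of not recording minor somatic events is kept.
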